### **2.7.2 Demographic and medical data.**

Data to be extracted from the Sciensano database are a list of all nursing homes in Belgium with their RIZIV number, postal code, the capacity of each nursing home (number of beds), and suspected (CT and symptoms) and confirmed (PCR and AG POC test) COVID-19 related death rate.

At the NH level, the management will be asked, at baseline, about the proportion of care grade (according to the Katz evaluation scale) among their residents, if a COVID-19 vaccination campaign was organized in the NH yet (date, type of vaccine and vaccination coverage), the suspected and confirmed COVID-19 infection rate, the COVID-19 related and non-COVID-19 related death rate from the beginning of the crisis until now and if and when they had an outbreak (more than one COVID-19 infection that are suspected to be related). With every follow-up sampling timepoint, the NH will be asked about a vaccination campaign (when this did not take place yet at baseline), if COVID-19 testing was performed in their NH, the respective proportion of positive tests and COVID-19 related death rate.

Individual medical data, comprising medical history and if participants have experienced an episode of COVID-19 symptoms or underwent a COVID-19 (PCR/antigen) test (with mention of date and result) or if COVID-19 was confirmed by a CT-scan, reason of missing data of drop outs (death, hospitalisation, sick leave, leaving the job), and whether they received a COVID-19 vaccination (date, type of vaccine, number of doses) in both NH residents and staff will be collected through an online questionnaire at both baseline and follow-up sampling timepoints (LimeSurvey) (See Appendix 6.3 for questionnaires). The CRC will fill out the questionnaire concerning the resident participants during the week of the sampling timepoint. Therefore the head of the nursing staff or the representative of the resident can be asked to provide the data. In this questionnaire, the surveyed medical data will be linked to the participant identification code. Concerning the medical history, the participants (NH staff and residents) will be asked

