for COVID-19 relevant preconditions: cardiovascular diseases, diabetes, hypertension, serious heart, lung or renal diseases, immunosuppressing conditions or medication and any form of active cancer. Furthermore, participants (staff and residents) will be asked if they received a COVID-19 vaccination (date, type of vaccine, number of doses), underwent a PCR-/ antigen-test, the date of this test and the result (if more than one test was performed, the date of the first positive test has to be given) or if COVID-19 was confirmed by a CT-scan, and, if they experienced COVID-19 symptoms and when (date). The COVID-19 symptoms episode will be defined according to the Sciensano case definition:

- At least one of following acute principal symptoms not explained by another clear cause: coughing, dyspnoea, chest pain, sudden loss of olfactory sense and/or taste;

OR

- At least two of following symptoms not explained by another clear cause: fever, myalgia, tiredness, rhinitis symptoms, sore throat, head ache, anorexia, diarrhoea, acute confusion, sudden collapse

OR

- Worsening of chronic respiratory symptoms (COPD, asthma, chronic cough) not explained by another clear cause

Additionally, staff members are asked questions concerning vaccine hesitancy (if and why they hesitated to get vaccinated against COVID-19), see Appendix 6.3.

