### **Secondary objectives**

4. To assess the seroprevalence according to vaccination status among NH residents and staff in Belgium at month 0 and at every follow-up visit in the cohort at month 2, 4, 6, 8 and 10.

The seroprevalence among NH residents and staff in Belgium at month 0, and follow-up in the cohort at month 2 (and if relevant at month 4, 6, 8, and 10), will be reported according to the vaccination status (Number of shots: 0, 1 or 2) and for the subgroups ‘with’ and ‘without’ a history of self-reported SARS-CoV-2 infection, averaged over NHs based on a GEE analysis with exchangeable covariance structure.

5. To assess the risk of getting a SARS-CoV-2 infection since vaccination between:
  - Residents and staff
  - Seropositive and seronegative participants at all timepoints
  - Individuals with or without previous self-reported SARS-CoV-2 infections
  - Adjusted for the updated vaccination degree of NH at all timepoints

For vaccinated participants only, a survival analysis will be performed to investigate the time (in days) to a SARS-CoV-2 infection since vaccination between sero-positive and -negative

participants at all time points. A participant is considered to have an event when the participant had a positive PCR test result (or a positive antigen rapid test, or a positive CT scan, or a positive saliva test in absence of a PCR test). The survival or censoring time (in days) is registered since 14 days after being fully vaccinated (full dose regimen) until first event (or censoring moment). If the proportional hazard assumption holds, a stratified (by NH) Cox proportional hazards regression model will be used to model the hazard of SARS-CoV-2 infection between sero-positive and -negative participants at all time points (modelled by the inclusion of a time-varying seropositivity status), adjusted for type of participant, history of self-reported SARS-COV-2 infections, and a time-varying NH vaccination degree. The analysis will be performed stratified by type of participant or other variables, if the proportional hazard assumption does not hold.

6. To assess the proportion of confirmed COVID-19 deaths and non-COVID-19 related deaths since vaccination and the time until death (within the study timeframe) between sero-positive and -negative participants for NH residents

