### **Tertiary objectives**

Although this study was not designed to assess vaccine effectiveness, end points will be compared between vaccinated and non-vaccinated participants, applying propensity score methods, if sufficient non-vaccinated participants occur in the random selected sample.

8. To assess the risk of getting SARS-CoV-2 infected between vaccinated and non-vaccinated (at last visit) residents/staff.

If a sufficient number of non-vaccinated participants are available in the sample, a survival analysis will be performed to investigate the time (in days) to a SARS-CoV-2 infection

since 14 days after being fully vaccinated between vaccinated and non-vaccinated participants. A participant is considered to have an event when the participant had a reported positive PCR test result (or a positive antigen rapid test, or a positive CT scan, or a positive saliva test in absence of a PCR test) during the baseline or one of the follow-up visits. The survival or censoring time (in days) is registered since 14 days after being fully vaccinated (or since 14 days after main (second) vaccination date in corresponding NH in case of non-vaccinated participants) until first event (or censoring moment).

If the proportional hazard assumption holds, a stratified (by NH) Cox proportional hazards regression model will be used to model the hazard of SARS-CoV-2 infection between staff and residents, and between vaccinated and non-vaccinated participants, adjusting for history of self-reported SARS-COV-2 infections, and a time-varying NH vaccination degree. Propensity score methods will be applied to reduce the effects of confounding. If insufficient non-vaccinated residents would be available in the cohort, the analysis will be performed for staff only.

9. To assess the proportion of confirmed COVID-19 deaths and non-COVID-19 related deaths and the time until death (within the study timeframe) between vaccinated and non-vaccinated residents.

If sufficient non-vaccinated residents would be available, a survival analysis will be performed to investigate the time (in days) to a confirmed COVID-19 death since 14 days after vaccination (or since 14 days after main (second) vaccination date in corresponding NH in case of non-vaccinated participants). A non-COVID-19 related death will be considered as a competing risk in the analysis.

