## Individuele vragenlijst (in te vullen bij aanvang studie)

### **Versie voor deelnemende medewerkers:**

1. Gelieve uw uniek studienummer in te vullen. (cfr lijst met random cijfers en studienummers, terug gestuurd door het onderzoekscentrum UGent)
2. Gelieve uw leeftijd in te vullen.
3. Wat is uw geslacht? M/V
4. Wat is uw functie (hoofdactiviteit) binnen het WZC
  - Zorg
  - Administratie
  - Paramedisch (kinesitherapeut, ergotherapeut, ...)
  - Poetswerk
  - Keuken
  - Kapper/pedicure
  - Andere (vrijwilliger, animatie, ...): (*Invulmogelijkheid*)
5. Werkt u op een afdeling voor bewoners met dementie? Ja / neen
6. Lijdt u aan 1 van volgende aandoeningen? Duid aan wat van toepassing is (meerdere antwoordmogelijkheden).
  - Hart- en vaatziekten
  - Diabetes
  - Hoge bloeddruk (hypertensie)
  - Ernstige long-/hart-/nierziekte
  - Verzwakt immuunsysteem (immunosuppressieve aandoeningen) of immuunsysteem verzwakt door langdurig gebruik van immunosuppressieve medicatie (vb. chemotherapie, transplantatiepatiënten, immunosuppressieve reumamedicatie, corticoïden...)
  - Actieve kankeraandoening
  - Geen van bovenstaande
- Bent u gevaccineerd tegen COVID-19?
  - Ja, 1 dosis
  - Ja, 2 dosissen
  - Neen
  - Zo ja, welk vaccin kreeg u toegediend
    - Het AstraZeneca/Oxford vaccin
    - Het BioNtech-Pfizer vaccin
    - Het Moderna vaccin
    - andere
  - Zo ja, datum van vaccinatie (eerste spuit).

7. Bent u dit seizoen gevaccineerd tegen griep? (*Deze vraag zal terugkomen in de vragenlijst bij laatste follow-up*)
8. Bent u ooit getest geweest op het coronavirus (via PCR/ag-sneltest/of radiologisch via CT-scan)? Ja/Nee
9. Zo ja, Bent u ooit **positief** getest geweest op het coronavirus? (Meerdere antwoordmogelijkheden)
  - Ja, via PCR-test (test waarbij men via een neuswisser een staal afneemt en u na labo-analyse het resultaat krijgt)
  - Ja, via antigeen sneltest (test waarbij men via neuswisser een staal afneemt en men binnen het kwartier het resultaat kan aflezen)
  - Ja, radiologisch, via een CT-scan
  - neen
9. Zo ja, datum van 1ste positieve PCR-test of sneltest (bij benadering)?
10. Indien COVID-19 radiologisch bevestigd werd via een CT-scan, vermeld de datum van deze CT-scan.
11. Indien u ooit positief getest bent, waar lag de vermoedelijke bron van besmetting?
  - Binnen het WZC
  - Buiten het WZC
  - De bron van de besmetting was mij onbekend

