**Versie voor deelnemende medewerkers:**

1. Gelieve uw uniek studienummer in te vullen.
2. Neemt u nog deel aan de studie (zal deze vragenlijst vervolledigd worden) ?  
Zo neen, waarom niet?

*Door de onderzoeker in te vullen*

- a. Tussentijdse afwezigheid in de studie (ziekte, vakantie, hospitalisatie ...)
- b. Deelnemer wenst niet meer deel te nemen
- a. Vermoedelijk of bewezen COVID-19 overlijden                      datum van overlijden:
- b. Niet-COVID-19 gerelateerd overlijden                      datum van overlijden:
- c. Medewerker is niet langer werkzaam in het WZC

*Vraag 3 wordt enkel toegevoegd indien voordien neen werd geantwoord.*

3. Bent u gevaccineerd tegen COVID-19?
  - a. Ja, 1 dosis
  - b. Ja, 2 dosissen
  - c. Neen
  - d. Zo ja, welk vaccin kreeg u toegediend
    - i. Het AstraZeneca/Oxford vaccin
    - ii. Het BioNtech-Pfizer vaccin
    - iii. Het Moderna vaccin
    - iv. andere
  - e. Zo ja, datum van vaccinatie (eerste spuit).
4. Bent u in de afgelopen twee maanden getest geweest op het coronavirus (via PCR/ag-sneltest/of radiologisch via CT-scan)? Ja/Nee
5. Zo ja. Bent u in de afgelopen 2 maanden (tussen de vorige testronde en nu) positief getest?  
*Meerdere antwoordmogelijkheden*
  - Ja, via PCR-test (test waarbij men via een neuswisser een staal afneemt en u na labo-analyse het resultaat krijgt)
  - Ja, via antigeen sneltest (test waarbij men via een neuswisser een staal afneemt en men binnen het kwartier het resultaat kan aflezen)
  - Ja radiologisch, via een CT-scan
  - neen
6. Zo ja, datum van 1ste positieve PCR-test of sneltest in de afgelopen 2 maanden (bij benadering)?

7. Indien COVID-19 radiologisch bevestigd werd via een CT-scan , vermeld de datum van deze CT-scan.
8. Hebt u in de afgelopen 2 maand (tussen de vorige testronde en nu) een periode 1 of meerdere van volgende symptomen ervaren, zonder dat hier een duidelijke verklaring voor was? Duid aan wat van toepassing is (meerdere antwoordmogelijkheden).
  - Hoest
  - Kortademigheid
  - Pijn op de borst
  - Smaakverlies
  - Geurverlies
  - Verergering van chronische respiratoire aandoeningen (vb. COPD, astma, chronische hoest,...)
  - Koorts
  - Spierpijn
  - Vermoeidheid
  - Loopneus/verstopte neus
  - Keelpijn
  - Hoofdpijn
  - Verlies van eetlust
  - Diarree
  - Acute verwardheid
  - Plotse val
9. Zo ja, wanneer hebt u, bij benadering, deze symptomen ervaren? Gelieve de dag aan te geven waarop deze symptomen zijn begonnen.

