### **Versie voor deelnemende bewoners**

*(in te vullen door de onderzoeker; bevragen bij de (hoofd)verpleegkundige of de vertegenwoordiger van de bewoner):*

1. Gelieve het uniek studie nummer van de deelnemer in te vullen.
2. Neemt de bewoner nog deel aan de studie (zal deze vragenlijst vervolledigd worden)?  
ja/neen  
Zo neen, waarom niet?
  - a. Vermoedelijk of bewezen COVID-overlijden (datum overlijden)
  - b. Niet-COVID-19 gerelateerd overlijden (datum overlijden)
  - c. Bewoner wenst niet meer deel te nemen

*Vraag 3 wordt enkel toegevoegd indien voordien neen werd geantwoord.*

3. Is bewoner gevaccineerd tegen COVID-19?
  - a. Ja, 1 dosis
  - b. Ja, 2 dosissen
  - c. Neen
  - d. Zo ja, welk vaccin werd toegediend
    - i. Het AstraZeneca/Oxford vaccin
    - ii. Het BioNtech-Pfizer vaccin
    - iii. Het Moderna vaccin
    - iv. andere
  - e. Zo ja, datum van vaccinatie (eerste spuit).
- 4.

5. Is de deelnemer in de afgelopen twee maanden getest geweest op het coronavirus (via PCR/ag-sneltest/of radiologisch via CT-scan)? Ja/Nee
6. Zo, ja. Is de deelnemer in de afgelopen 2 maand (tussen de vorige testronde en nu) **positief** getest op het coronavirus?
  - Ja, via PCR-test (test waarbij men via een neuswisser een staal afneemt en u na labo-analyse het resultaat krijgt)
  - Ja, via antigen sneltest (test waarbij men via neuswisser een staal afneemt en men binnen het kwartier het resultaat kan aflezen)
  - Ja, radiologisch, via een CT-scan
  - Neen
7. Zo ja, datum van 1ste positieve PCR-test of sneltest de voorbije 2 maanden (bij benadering)?
8. Indien de COVID-19 radiologisch bevestigd werd via een CT-scan, vermeld de datum waarop dit is gebeurd.
9. Heeft de deelnemer in de afgelopen 2 maand (tussen de vorige testronde en nu) een periode 1 of meerdere van volgende symptomen ervaren, zonder dat hier een duidelijke verklaring voor was? Duid aan wat van toepassing is (meerdere antwoordmogelijkheden).
  - Hoest
  - Kortademigheid
  - Pijn op de borst
  - Smaakverlies
  - Geurverlies
  - Verergering van chronische respiratoire aandoeningen (vb. COPD, astma, chronische hoest,...)
  - Koorts
  - Spierpijn
  - Vermoeidheid
  - Loopneus/verstopte neus
  - Keelpijn
  - Hoofdpijn
  - Verlies van eetlust
  - Diarree
  - Acute verwardheid
  - Plotse val
10. Zo ja, wanneer heeft de deelnemer, bij benadering, deze symptomen ervaren? Gelieve de dag aan te geven waarop deze symptomen zijn begonnen.

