#### **Version pour les employés participants:**

18. Veuillez saisir votre numéro d'étudiant unique.
19. Participez-vous toujours à l'étude (ce questionnaire sera-t-il rempli)?

Sinon, pourquoi pas?

*À compléter par le chercheur*

- c. Absence provisoire de l'étude (maladie, vacances, hospitalisation ...)
- d. Le participant ne souhaite plus participer
- a. Mort suspectée ou prouvée de COVID-19 Date de décès:
- b. Décès non liés au COVID-19 Date de décès:
- c. L'employé ne travaille plus au WZC

*La question 20 n'est ajoutée que si la réponse était non auparavant.*

20. Avez-vous été vacciné contre le COVID-19?

- Oui, une dose
- Oui, deux doses
- Non

- o Si oui, quel vaccin vous a-t-il administré
    - ☐ Le vaccin AstraZeneca / Oxford
    - ☐ Le vaccin BioNtech-Pfizer
    - ☐ Le vaccin Moderna
    - ☐ autre
  - o Si oui, date de vaccination (première seringue).
- 21.
22. Avez-vous été testé pour le coronavirus (via PCR / test rapide AG / ou radiologique via CT scan) au cours des deux derniers mois? Oui Non
23. Si c'est le cas. Avez-vous été testé positif au cours des 2 derniers mois (entre le cycle de test précédent et maintenant)? Plusieurs options de réponse
- Oui, via un test PCR (test dans lequel un échantillon est prélevé via un écouvillon nasal et vous obtenez le résultat après analyse en laboratoire)
  - Oui, via un test rapide d'antigène (test dans lequel un échantillon est prélevé via un tampon nasal et le résultat peut être lu en 15 minutes)
  - Oui radiologiquement, via un scanner
  - non
24. Si oui, date du 1er test PCR positif ou test rapide au cours des 2 derniers mois (approximative)?
25. Si le COVID-19 a été confirmé radiologiquement par un scanner, indiquez la date de ce scanner.
26. Au cours des 2 derniers mois (entre la précédente série de tests et maintenant), avez-vous ressenti un ou plusieurs des symptômes suivants pendant une période, sans aucune explication claire? Indiquez ce qui s'applique (options de réponses multiples).
- Toux
  - Essoufflement
  - Douleur thoracique
  - Perte de goût
  - Perte d'odeur
  - Aggravation des maladies respiratoires chroniques (ex: BPCO, asthme, toux chronique, ...)
  - Fièvre
  - fatigue musculaire
  - Fatigue
  - Nez qui coule / bouché
  - Gorge irritée
  - Mal de crâne
  - Perte d'appétit
  - La diarrhée
  - Confusion aiguë
  - Chute soudaine

27. Si oui, quand avez-vous ressenti ces symptômes? Veuillez indiquer le jour où ces symptômes ont commencé.

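### The infection event in objectives 5 and 8 counts a positive saliva test, but no individual questionnaire has a field to record or date one

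*Protocol*

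**What the plan says.** **Event definition.** In section 3.2, objective 5 (listed as the second secondary objective in section 2.1) analyses time to infection in vaccinated participants. The event is a positive PCR, a positive antigen rapid test, a positive CT scan, "or a positive saliva test in absence of a PCR test". Objective 8 (the first tertiary objective) uses the same four routes and ties them to what is reported at the study visits: "or a positive CT scan, or a positive saliva test in absence of a PCR test) during the baseline or one of the follow-up visits".

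**Data to be collected.** Section 2.7.2 says individual medical data come from the online questionnaire. On testing it lists whether the participant "underwent a COVID-19 (PCR/antigen) test (with mention of date and result) or if COVID-19 was confirmed by a CT-scan", and repeats the item as "underwent a PCR-/ antigen-test, the date of this test and the result". Saliva is not mentioned.

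**Forms.** In Appendix 6.3 the opening test question for staff at baseline is "Bent u ooit getest geweest op het coronavirus (via PCR/ag-sneltest/of radiologisch via CT-scan". At follow-up it is "Bent u in de afgelopen twee maanden getest geweest op het coronavirus (via PCR/ag-sneltest/of radiologisch via CT-scan" for staff and "Is de deelnemer in de afgelopen twee maanden getest geweest op het coronavirus (via PCR/ag-sneltest/of radiologisch via CT-scan" for residents. The French forms use the same three test types and describe PCR to the respondent as a "test dans lequel un échantillon est prélevé via un écouvillon nasal".

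**The concern.** The endpoint and the instrument that is meant to measure it are both printed in this protocol, and they do not match. One of the four stated routes to an event has no data item. This is therefore not a detail that could be left to a separate analysis plan: an analyst cannot derive a component that the forms never ask for.

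At stake is the event count in the time-to-infection analyses of objectives 5 and 8. A participant whose only positive result came from saliva may stay in the risk set as uninfected. Even if the result became known, no dedicated field would give the date needed for a survival time in days.

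**Working it through.** The plan gives no figure to reproduce. The check compares the event definition with every described source of individual test results.

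**1. Event definition against data items**

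| Event component (objectives 5 and 8) | Section 2.7.2 | Opening test question | Positive-result item | Date item |
|---|---|---|---|---|
| PCR | yes | yes | yes, described as nasal swab with laboratory analysis | yes |
| Antigen rapid test | yes | yes | yes, described as nasal swab | yes, shared with PCR |
| CT scan | yes | yes | yes | yes, separate |
| Saliva test | no | no | no | no |

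The pattern is the same in all 2 languages x 2 participant types x 2 occasions = 8 individual forms. In each, the only remaining answer to the positive-result item is no; none offers another test type.

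**2. Other sources.** The register extract described in section 2.7.2 holds nursing-home characteristics and death rates, not individual test results. No other individual source is described.

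**3. What happens to a saliva-positive participant**

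- No PCR, antigen test or CT in the period: the literal answer to the opening question is no, and the result and date items, which depend on a yes, do not apply. No event is recorded.
- A negative PCR, antigen test or CT in the period: the participant reaches the result item, where the literal answer is no. No event is recorded.
- The respondent or coordinator ticks PCR or antigen for the saliva test: an event is recorded, but under the wrong test type, and it cannot be identified as saliva.
- A positive PCR, antigen test or CT as well: the event is captured.

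The exposed set is therefore infections detected by saliva alone.

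**4. Effect on the estimates.** Let s be the share of first infections that are detected by saliva alone and go unrecorded. The documents give no value for s.

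- Recorded hazard is about (1 - s) x true hazard.
- Recorded hazard ratio, group 1 to group 2, is about true hazard ratio x (1 - s1)/(1 - s2).

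With assumed values only:

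| s1 | s2 | Multiplier on the hazard ratio |
|---|---|---|
| 0.05 | 0.05 | 0.95/0.95 = 1.00 |
| 0.20 | 0.20 | 0.80/0.80 = 1.00 |
| 0 | 0.05 | 1/0.95 = 1.05 |
| 0 | 0.20 | 1/0.80 = 1.25 |

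The first two rows lose 5% and 20% of events but leave the ratio roughly unchanged. The last two put all the loss in one group, which is the extreme case; swapping the groups gives the reciprocals, 0.95 and 0.80.

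**The case against.** The strongest reply is that the gap is small and its consequence unproven. Much of this stands.

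- **The forms need not fail every time.** The nasal-swab wording is a bracketed lay explanation, and someone with a laboratory-analysed saliva sample may tick PCR. Resident forms are completed by the research coordinator with the head nurse or representative, so a mechanical no is less certain there. A reader might infer that a saliva event can never enter the data; the documents support only that it is not reliably captured or identifiable.
- **The affected set is residual.** Anyone also positive by PCR, antigen test or CT is counted, and nothing in the protocol shows how far saliva testing was used in these homes.
- **Bias is conditional.** A reader might infer that the resident-versus-staff comparison is biased because staff are screened more often by saliva. The protocol describes no such screening. Nor does it suggest that saliva testing differs by serostatus, the main contrast in objective 5.
- **Infection history.** A reader might also infer that saliva-only cases are later misclassified as having no history of infection. The history covariate is not defined to include saliva and is not described as time-varying, so the text does not establish this.
- **Nursing-home forms.** The follow-up forms also count only PCR and antigen tests, but these facility totals do not feed the individual endpoint.
- **Reach.** Objective 8 runs only if there are enough non-vaccinated participants, and both primary objectives rest on the study's own antibody test.

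None of this supplies the missing item. Ticking another test type for a saliva result is itself an unplanned misclassification.

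**Conclusion.** The mismatch is certain. Objectives 5 and 8 name a saliva test as an event, and neither section 2.7.2 nor any individual form provides a way to record or date one. Infections detected by saliva alone are either left event-free or filed under another test type.

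The size is unknown, because the documents give no share of such infections. With similar shares in the compared groups, only events and precision are lost; with different shares, the hazard ratio moves by about (1 - s1)/(1 - s2). The multipliers above rest on assumed shares and on the approximation that unrecorded infections thin the hazard proportionally. They are illustrations, not estimates, and the range includes no bias.

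The effect is confined to a residual component of one secondary and one conditional tertiary objective, so severity is minor.

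**What to change.** Preferably, add saliva test to the opening test question, the list of positive-test types and the date item in all eight individual forms, in both languages, and add it to the individual data listed in section 2.7.2. At the next round, ask once about any earlier positive saliva test and its date, and state how rounds collected without the item are handled.

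If the forms cannot be changed, delete the saliva component from the event definitions of objectives 5 and 8, so that the stated endpoint is the one measured.

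The cost is a minor amendment to an online questionnaire whose staff follow-up version was already being extended with the vaccine-hesitancy items, plus some recall error in the catch-up answers. Deletion costs nothing in data collection, but it gives up any infection detected by saliva alone.
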